# Comparing two strategies to support the implementation of evidence-based practices for substance use disorders in VA’s permanent supportive housing program: a protocol for a type 3 hybrid cluster-randomized controlled trial

**DOI:** 10.1186/s13012-026-01498-z

**Published:** 2026-03-24

**Keywords:** Substance use disorders, Permanent supportive housing, Homelessness, Implementation science, Veterans

## Abstract

**Background:**

Homeless-experienced Veterans (HEVs) have higher rates of substance use disorders (SUDs) than housed Veterans, which impairs their ability to retain housing. The Department of Housing and Urban Development-VA Supportive Housing (HUD-VASH) initiative, which provides subsidized permanent housing and supportive services, contributed to the 50% reduction in Veteran homelessness over the past decade. However, ~ 40% of Veterans exit HUD-VASH within two years, often due to untreated SUDs. We will use two strategies to support the implementation of Medications for Addiction Treatment (MAT) and Cognitive Behavioral Therapy for Substance Use Disorders (CBT-SUD) in 12 HUD-VASH sites; conduct an evaluation of this implementation effort; and generate an implementation playbook to support continued spread of MAT and CBT-SUD in HUD-VASH.

**Methods:**

We will use Replicating Effective Programs (REP) to implement MAT and CBT-SUD at 12 sites over 18 months. After 9 months of REP alone, half (n = 6) of these sites will also receive Consumer Engagement (CE) for 9 months, activating HEVs to adopt these practices via peer coaching. We will conduct a type 3 hybrid cluster-randomized trial to compare the impacts of REP versus REP + CE. Randomization will occur at two levels: implementation start date (3 cohorts) and the implementation strategy (REP versus REP + CE). We will use stratified block randomization to balance site size among sites receiving each strategy across cohorts. We will use mixed methods to assess the impacts of REP versus REP + CE on implementation outcomes (reach [primary outcome], adoption, and sustainment); Veteran outcomes (primarily housing); provider and Veteran experiences; and costs and budget impacts. We hypothesize that REP + CE will have higher implementation costs than REP but result in improved MAT and CBT-SUD implementation and Veteran outcomes, leading to a business case for REP + CE.

**Discussion:**

Implementing MAT and CBT-SUD within HUD-VASH can improve HEVs’ housing and health. By identifying effective strategies to support the implementation of these practices, we aim to inform other implementation efforts of behavioral health practices in homeless service settings.

**Trial registration:**

This project was registered with ClincialTrials.gov as “Coordinated Access for Addiction Recovery and Equity in VA Supportive Housing.” Trial registration NCT07141394, registered 8/26/2025 (https://clinicaltrials.gov/study/NCT07141394?term=CARE-VASH&rank=1).

Contributions to the literature
This protocol uses tailored and data-driven implementation approaches to address inequities in the use of evidence-based practices for substance use disorders.This trial integrates a cluster-randomized design and mixed-methods evaluation to compare the impacts of a base versus enhanced implementation strategy on the implementation and effectiveness of two evidence-based substance use disorder practices.This study uses a robust methodologic framework to address disparities in the implementation of substance use disorder interventions in a complex, highly field-based social service setting.

## Background

Homeless-experienced Veterans (HEVs) have higher rates of substance use disorders (SUDs) than their housed counterparts [1], which impair their ability to retain housing. The Department of Housing and Urban Development-VA Supportive Housing (HUD-VASH) initiative—which provides subsidized, permanent housing and supportive services—has contributed substantively to the 50% reduction in Veteran homelessness over the past decade [2]. The program has housed ~180,000 Veterans since 2012 [3]. Yet, up to 40% of Veterans exit HUD-VASH within two years of housing [4]. Most of these exits represent returns to homelessness, with untreated SUDs as a common primary or contributing factor [5–8]. National implementation of evidence-based practices (EBPs) for SUDs within HUD-VASH would substantively advance VA’s commitment to end Veteran homelessness.

HUD-VASH is a “Housing First” program, in which Veterans receive independent, permanent housing with supportive services [9]. Housing First increases days in stable housing and decreases Emergency Department (ED) use and hospitalizations, without worsening SUDs [9]. Each HUD-VASH team is assigned to a VA medical center or clinic (i.e., VA healthcare system division); teams are interdisciplinary, led by a social worker and staffed by case managers, nurses, and peer supports, and serve Veterans largely in the field (e.g., home visits).

In our prior evaluation [10] for HEVs who attained HUD-VASH housing from 2018–2021 (n = 63,939), most had ≥ 1 SUD (66%, n = 42,182). Veterans with SUDs were 1.4 times more likely to have a negative exit from HUD-VASH within one year of move-in. Though nearly half (47.3%, n = 19,931) of HEVs with SUDs in HUD-VASH had ≥ 1 SUD specialty visit, receipt of EBPs for SUDs was low. In the year after HUD-VASH move-in, only 9.6% and 19.9% of Veterans with alcohol use disorder (AUD) and opioid use disorder (OUD), respectively, received ≥ 1 medication for addiction treatment (MAT) prescription [11]. This finding is concordant with a prior study of OUD in VA homeless programs, which describes gaps in MAT provision and asserts the importance of policy goals for addressing OUD among HEVs [12]. Moreover, among HEVs with stimulant use disorder (35.9% of HUD-VASH participants), < 0.5% received Cognitive Behavioral Therapy for SUDs (CBT-SUD) [10]. Therein, though the VA has implemented MAT and CBT-SUD within mental health clinics, HUD-VASH adoption is low. National implementation of evidence-based practices (EBPs) for SUDs within HUD-VASH can improve housing outcomes among homeless-experienced Veterans.

This paper describes the Coordinated Access for Addiction Recovery and Equity in VA Supportive Housing (CARE-VASH) Quality Enhancement Research Initiative (QUERI), which will implement MAT and CBT-SUD at 12 HUD-VASH sites and compare the impacts of two implementation strategies on implementation and effectiveness outcomes. To implement and sustain MAT and CBT-SUD across sites, we will use the Replicating Effective Programs (REP) bundle for 18 months, engaging diverse stakeholders (“Learning Community”) to package the EBPs; provide staff training; conduct evaluation; and support maintenance [13]. In addition to REP, 6 sites will receive 9 months of Consumer Engagement (CE). In CE, Veterans will be activated to use EBPs via a Veteran panel, educational materials, and HUD-VASH peer coaching.

Partnered with VA mental health and homeless service leaders, our Specific Aims are to: 1) Use REP and REP + CE to support the implementation and sustainment of MAT and CBT-SUD in 12 HUD-VASH sites; 2) Compare, in a type 3 hybrid implementation-effectiveness trial, the impacts of REP versus REP + CE on MAT and CBT-SUD reach, adoption, and sustainment; Veteran outcomes and provider experiences; and costs and budget impacts; and 3) Generate an implementation playbook for program partners to support continued spread and sustainment of MAT and CBT-SUD in HUD-VASH.

## Methods

### Overview

We will conduct a cluster-randomized trial comparing sites (or clusters) randomized to REP versus REP + CE. Specifically, we will conduct a type 3 hybrid implementation-effectiveness trial [14] using a stepped wedge design with randomization at two levels: implementation start date (3 cohorts) and implementation strategy (REP vs. REP + CE). We will use stratified block randomization to balance site size among sites receiving each strategy across cohorts. We will use mixed methods to assess the impacts of REP vs. REP + CE. We hypothesize that REP + CE will have higher implementation costs than REP, but result in improved and more equitable EBP reach, adoption, sustainment, and housing outcomes, leading to a business case for REP + CE.

### Conceptual framework

CARE-VASH is guided by the Health Equity Implementation Framework [15] (HEIF, Fig. 1), which identifies how contextual and societal factors influence EBP implementation and address disparities. HUD-VASH encounters are conceptualized as the confluence of interactions between HEVs, EBPs, and HUD-VASH teams. These interactions are nested within healthcare system and community-level contexts. These factors interplay with strategies that support EBP implementation to enhance equity by addressing disparities created by structural inequities.

**Fig. 1 Fig1:**

Health equity implementation framework (HEIF), specified for MAT and CBT-SUD implementation in HUD-VASH. HEV = Homeless-experience veterans. EBPs = Evidence-based practices. REP = Replicating effective programs. MAT = Medications for addiction treatment. CBT-SUD = Cognitive behavioral therapy for substance use disorders

### Medications for Addiction Treatment (MAT)

Medications for Alcohol Use Disorder (MAUD) and Medications for Opioid Use Disorder (MOUD) are implementation priorities within VA primary care and mental health but have not been systematically incorporated in HUD-VASH. MAUD includes naltrexone and acamprosate. Across meta-analyses and systematic reviews, MAUD resulted in significantly decreased alcohol consumption compared to placebo [16, 17]. In a meta-analysis [16] of 118 randomized controlled trials (RCT), the number needed to treat (NNT) to prevent return to drinking was 11 for acamprosate and 18 for oral naltrexone. Injectable naltrexone was significantly associated with reduced drinking days (weighted mean difference [WMD] −5 days).

MOUD includes methadone, buprenorphine, and extended-release naltrexone. In a meta-analysis of 11 RCTs [18], methadone was significantly more effective than placebo or non-pharmacological treatments on treatment retention (risk ratio [RR] 4.44) and the reduction of morphine-positive urine or hair analysis (RR 0.66). In a meta-analysis of 31 RCTs, buprenorphine was significantly more effective than placebo on treatment retention at low (RR 1.5); medium (RR 1.74); and high (RR 1.82) doses. In an RCT [19] comparing extended-release naltrexone to counseling, relapse was significantly lower in the naltrexone group (43% vs. 64%) over 24 weeks. Buprenorphine and methadone significantly reduce mortality [20], opioid-related overdoses and acute care [21].

### Cognitive Behavioral Therapy for Substance Use Disorders (CBT-SUDs)

CBT-SUD is an evidence-based psychotherapy used across SUDs [22, 23]. It is delivered in 12–16 sessions by mental health providers in individual or group sessions (in-person or virtual), addressing maladaptive interactions among thoughts, emotions, and substances [24]. A meta-analysis and systematic review demonstrate that CBT-SUD reduces frequency and quantity of use [25, 26]. Among Veterans, CBT-SUD is associated with improvements in personal relationships [27].

The strength of evidence for CBT-SUD is bolstered by evidence demonstrating its mechanism of action (e.g., improved self-efficacy). In VA’s CBT-SUD Training Program (in specialty mental health, not homeless programs), 457 Veterans enrolled in CBT-SUD [24]. Among these Veterans, intent-to-treat analyses showed > 50% reduction in heavy drinking and other drug use; 29% reduction in craving days; 47% reduction in substance use related problems; and improvements in quality of life.

### Implementation strategy: Replicating Effective Programs (REP)

CARE-VASH QUERI will use REP at 12 HUD-VASH sites to implement MAT and CBT-SUD. REP engages stakeholders to package EBPs and their associated training materials; it is the go-to implementation strategy for VA mental health EBPs but has not been used routinely in HUD-VASH [24]. Our use of REP is intended to enhance HUD-VASH providers’ skills and clinical competency, enhancing MAT and CBT-SUD reach, adoption, and sustainment. REP is well-suited for EBP implementation in HUD-VASH; adapting and packaging EBPs and associated trainings for program and population contexts, using stakeholder input, is critical for effective implementation in homeless service settings [28].

Table 1 summarizes REP’s phases in CARE-VASH. In REP phase one (“pre-conditions”), completed prior to this proposal, MAT and CBT-SUD were identified as preferred EBPs for implementation in meetings with our national VA mental health and homeless program partners. The first year of CARE-VASH will encompass REP phase two (“pre-implementation”) and will engage a Learning Community (national, interdisciplinary, and multi-level stakeholders, including HEVs with SUDs, providers and managers, and regional/national representatives from our partners). We will work with the Learning Community to package training materials; orienting HUD-VASH sites to these EBPs and planning for logistics; and assessing and refining process and outcome metrics for our evaluation. Nationally, our VA mental health partner has training paradigms for both EBPs: academic detailing (AD) for MAT and technical assistance (TA) for CBT-SUD. As these are considered the lowest level of implementation support that can result in adequate MAT and CBT-SUD adoption, we will use REP to adapt AD and TA to fit the needs of HUD-VASH. REP phase three (“implementation”) includes delivery of the MAT and CBT-SUD packages to 12 HUD-VASH sites, with refinement informed by our evaluation [29]. REP phase four (“maintenance”) will be iterative throughout CARE-VASH, anchored in our evaluation, including assessing financial factors and organizational changes needed for EBP sustainment. We will engage the Learning Community to develop a final implementation playbook, including strategies for ongoing evaluation and improvement, that can be used for national spread and sustainment by our partners.

**Table 1 Tab1:** Replicating effective program (REP) phases, specified for CARE-VASH

Pre-conditions	Pre-implementation	Implementation	Maintenance
Select EBPs, identify implementation barriers, and engage Learning Community to draft implementation packages (e.g., adapting Academic Detailing [AD] for MAT; CBT-SUD training & technical assistance [TA])	Develop implementation packages, using AD and TA, with the Learning Community; orient sites to EBP implementation; refine process and outcome metrics	Train and fill knowledge gaps among HUD-VASH staff; conduct implementation evaluation; refine both EBPs’ implementation packages	Re-organize packages for both EBPs with Learning Community, aiming for EBP spread and sustainment, identifying organizational and financial prerequisites for spread

#### REP specified for MAT implementation

Since low MAT adoption has been attributed in part to clinicians’ knowledge and training gaps—and AD trains clinicians in the use of novel evidence-based medications—AD will be incorporated into REP for MAT. AD uses 1:1 or small group training, audit-and-feedback tools, and clinician-targeted handouts to influence clinicians to use EBPs. These materials will be available on an online CARE-VASH toolkit once finalized. Current VA dashboards (detailing eligible patients by provider and by division) for MAT [30] will be adapted for HUD-VASH during REP pre-implementation. These dashboards will support educational outreach to prescribers (physicians and physician extenders) who treat HEVs in HUD-VASH with AUD and OUD. Outreach will be delivered by pharmacists trained in AD and with expertise in SUDs. Though the frequency and content of outreach will be determined during pre-implementation, we anticipate individual and small group virtual sessions with prescribers, employing scripts and messaging tailored for CARE-VASH. To enable sustainment, prescribers will be able to receive training from these pharmacists throughout CARE-VASH maintenance. Prescribers will use MAT with HEVs as part of their routine care of HEVs, which encompasses in-person and virtual individual visits, in the clinic or in the field (e.g., home visits). MAT is ideally delivered longitudinally as AUD and OUD are chronic illnesses.

#### REP specified for CBT-SUD implementation

Connecting intensive formal training to longer-term TA can enhance psychotherapy implementation [31, 32]. The specifics of CBT-SUD training and TA processes will be refined during pre-implementation; we anticipate that HUD-VASH case managers (social workers) who desire CBT-SUD training will first receive intensive CBT-SUD training: an asynchronous, individual web-based training from VA’s CBT-SUD mental health roll-out; and a one-day virtual, small group intensive CBT-SUD workshop on VA’s CBT-SUD protocol [31]. We anticipate that materials used for training will include existing VA videos and electronic materials available on internal VA servers along with adapted training materials (e.g., manuals, presentations) housed on VA servers through CARE-VASH. TA will follow, with weekly 1-h virtual small group case consultation sessions (for 4 months) moderated by CARE-VASH consultants who are social workers experienced in CBT-SUD to a train-the-trainer level. Case managers will deliver weekly CBT-SUD in individual or group sessions to HEVs on their caseloads for ~12 weeks, in person or virtually. Consultants will train case managers to attain fidelity via the CBT-SUD Rating Scale [31], defined as ≥ 80% fidelity for ≥ 6 consecutive sessions with ≥ 2 HEVs. Consultants will be available for as-needed virtual individual case consultation throughout REP. They will moderate virtual small group “booster consultations” (at 12 and 18 months) that use self-reflection to address drift away from high-fidelity practice [33]. During REP’s maintenance phase, all trained case managers and the consultants will join a Microsoft Teams group for asynchronous case discussion.

###  Implementation strategy: REP + Consumer Engagement (CE)

In addition to REP, 6 of the 12 sites will receive 9 months of CE, activating HEVs to enhance EBP adoption and sustainment. CE has been successfully used within VA in a mental health implementation effort [34]; it can increase trust among Veterans to mitigate disparities [14] for socially vulnerable groups. Particularly for these EBPs—which have well-established national VA behavioral health rollouts, but low HUD-VASH penetrance—we hypothesize substantive value in engaging HEVs to become active participants in HUD-VASH encounters. All CE will be led by trained HUD-VASH peer support specialists.

Table 2 depicts key components of CE [34]. We will develop a panel of Veterans in HUD-VASH in recovery from SUDs (n ~ 8–10), embedded within our Learning Community. We will recruit HEVs via HUD-VASH peer support leaders at participating sites. We will use gift cards to compensate panel members for all activities. During pre-implementation, we will work with the panel to refine existing Veteran-facing MAT and CBT-SUD materials, ensuring appropriateness to HEVs’ experiences and backgrounds. These materials will be available on the online CARE-VASH toolkit. We will work with the panel to develop materials to train HUD-VASH peers—building on their lived SUD expertise—to activate HUD-VASH Veterans to seek MAT and CBT-SUD from their providers at REP + CE sites. Over the implementation period, peers will work with HEVs with SUDs who are disengaged from SUD care, providing coaching and education. We anticipate engaging peers in two interactive virtual training sessions (2 h each) on CE. After CE launches, we plan biweekly virtual learning collaboratives (60 min/group session) over 9 months, to foster knowledge sharing among peers regarding coaching and CE. To plan for sustainment, we will finalize our CE package, including HUD-VASH peer and Veteran toolkits.

**Table 2 Tab2:** Consumer engagement (CE), specified for CARE-VASH

Involve HEVs in implementation activities	Intervene with HEVs to enhance adoption and adherence to EBPs	Prepare HEVs to be active participants in HUD-VASH	Increase HEV demand for EBPs	Disseminate information about innovations
Build HEV panel, embedded in Learning Community, to inform CE strategy	Work with HEV panel and Learning Community to refine HEV-facing educational materials about EBPs; train peers	Peers activate HEVs to engage in HUD-VASH encounters around SUD services	Peers coach HEVs about MAT and CBT-SUD; distribute HEV-facing materials	Finalize CE package, including peer and Veteran toolkit, with Learning Community input (including HEVs)

### Participating sites

We identified 12 geographically diverse HUD-VASH implementation sites; each is nested in a division of a VA healthcare system and is comprised of ≥ 1 HUD-VASH team. Collectively, these sites serve ~7908 HEVs/year. Each site will implement MAT and CBT-SUD. Of note, our sample size (12 sites) was pre-determined by our funder.

### Study design

We plan a type 3 hybrid implementation-effectiveness trial [14], registered as NCT07141394 on 8/26/2025 and determined to be non-research by VA’s Central Institutional Review Board. We will use stratified block randomization, stratified by tertiles of each site’s number of HUD-VASH full-time equivalent (FTE) employees (proxy for size and resources).

Within the 12 sites, we will use a stepped wedge cluster randomized trial design [35] (Fig. 2) to study implementation outcomes, balanced for allocation to treatment timing and assignment to REP vs. REP + CE arms across 3 strata of 4 sites each (Fig. 3). Using a random number generator with assignment by our statistician, each stratum will be randomly assigned to 1 of 3 possible cohort pairings (cohorts 1 & 2; 2 & 3; 1 & 3). Within each stratum, 4 sites will be randomly assigned to 1 of the 2 cohorts in the pair, ensuring that there are early and late treatment timings within each stratum. Within each stratum-cohort combination (n = 2), the REP vs. REP + CE implementation strategy arm will be randomly assigned, and consent obtained thereafter. The staggering of sites into cohorts is necessary to provide HUD-VASH sites with optimal EBP and CE training within our resources. We selected the 9-month duration of REP, before augmenting with 9 months of CE at REP + CE sites, because we found this duration of REP to be effective in prior trials of a psychosocial EBP for HEVs [36]. We will be unable to blind sites (clusters) assigned to CE augmentation, as we need to engage with leadership regarding peer supports’ commitments. To optimize power in our effectiveness analyses, we will compare sites that receive REP vs. REP + CE vs. all other HUD-VASH sites in the nation that are not engaged in CARE-VASH.

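### Consent is placed after the arm draw: if it is the site's consent, refusal can depend on the arm, and analysis of all 12 sites as assigned is not fixed consistently

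*Protocol article*

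**What the plan says.** All of the design statements are in the protocol article.

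- **Order of steps (Study design).** Within each stratum-cohort block of two sites, the "implementation strategy arm will be randomly assigned, and consent obtained thereafter". The consenting party and the object of the consent are not named. The same section reports that the project was classed as non-research.
- **Blocks (Study design).** Allocation is balanced "across 3 strata of 4 sites each", and within a stratum the "4 sites will be randomly assigned to 1 of the 2 cohorts in the pair".
- **Allocation (section on REP + CE).** "6 of the 12 sites will receive 9 months of CE".
- **Sites (Participating sites).** "We identified 12 geographically diverse HUD-VASH implementation sites", and "our sample size (12 sites) was pre-determined by our funder". No agreement to accept either arm is mentioned.
- **Knowledge of the arm (Study design).** "We will be unable to blind sites (clusters) assigned to CE augmentation". The reason given is that leadership must be approached about what the peers will commit.
- **Load of CE (section on REP + CE).** "All CE will be led by trained HUD-VASH peer support specialists". The peers attend two 2-hour trainings and 60-minute collaboratives every second week for 9 months, besides the coaching itself.
- **Analysis groups.** Study design, the sustainment sentence under reach, adoption and sustainment, the opening of the housing outcome, and Acute care use all define the arms by the strategy sites receive or received. The housing regression model uses an indicator of site assignment.

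**The concern.** A cluster that agrees to take part only after learning its arm can let the arm influence its decision. The two arms do not ask the same of a site: CE draws on the site's own peers for 9 months, and REP alone does not. Identifying 12 sites is not the same as having each of them committed to whichever arm it draws.

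If a CE site declines or delays and is then dropped, replaced or moved to the REP group, the sites compared as REP + CE are no longer those that chance put there. What is at stake is the REP versus REP + CE contrast, the trial's randomised comparison of strategies. The comparison of either strategy with the period before the programme is not what the arm draw protects.

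Knowledge of the arm also comes early. The staff interview plan samples three peers per REP + CE site and interviews by cohort at baseline, so the arm has to be known 9 months before CE starts. The shared REP-only phase therefore does not conceal the allocation.

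**Working it through.** **1. Reproduce the design count.** Inputs from Study design: 3 strata, 2 cohorts per stratum, 2 sites per stratum-cohort block.

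3 × 2 × 2 = 12 sites, that is 6 blocks of 2. One site per arm in each block gives 6 REP and 6 REP + CE, as the article states.

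**2. How much slack there is.** Given the blocks, the number of possible arm allocations is 2^k for k complete blocks, and the smallest two-sided randomisation p-value is 2/2^k.

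| Complete blocks | Allocations | Smallest p |
|---|---|---|
| 6 | 64 | 0.031 |
| 5 | 32 | 0.0625 |
| 4 | 16 | 0.125 |

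The article does not plan a randomisation test. The table only shows how little the randomisation can spare.

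**3. Chance of at least one refusal.** The documents give no refusal rate. Assume a probability q for each of the 6 CE sites, independently: P = 1 − (1 − q)^6.

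| q (assumed) | P(at least one of 6) |
|---|---|
| 5% | 27% |
| 10% | 47% |
| 20% | 74% |
| 30% | 88% |

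**4. What a refusal does under each analysis.**

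- *Kept as assigned.* Reach is taken from VA administrative data, so outcomes could still be collected at a site that declines CE. There is then no selection. If one of six CE sites goes without CE, and sites have equal weight and a common effect, the effect is diluted to 5/6 = 0.83 of its value.
- *Excluded, replaced or analysed by strategy received.* The composition of the CE arm then depends on who refused. The direction and size depend on how refusing sites differ.

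**5. Why no size of bias is given.** A raw calculation is possible. Read rho = 0.04 as a between-site correlation, with 9.9% baseline reach for alcohol medication: site SD = √(0.04 × 0.099 × 0.901) = 0.060, or 6.0 points. Dropping one of six sites that lies 1 SD below the arm mean moves that mean by 1/5 SD = 1.2 points; dropping two moves it by 2/4 SD = 3.0 points. Three things prevent its use as the bias:

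- The reach and adoption model has site fixed effects, which remove stable differences in level between sites. Bias there would need refusal linked to trend or to response to the strategy, for which no figure is given.
- Sample size and power defines rho as a correlation of outcomes within a site over time, not between sites.
- The number of refusing sites and their distance from the mean are arbitrary.

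A raw shift in level could at most concern sustainment, which is measured cross-sectionally 9 months after each cohort ends.

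**The case against.** The strongest reply is that site refusal is inferred. The article does not say that a site may withdraw on learning its arm. The project is classed as non-research and the primary outcome comes from administrative data, so the consent could be that of the staff and Veterans who are interviewed. Site agreements are also the kind of detail an article leaves to a fuller document. This stands in part: the point is conditional on the consent being the site's. It does not remove the point, because the order of draw and consent is stated outright and the leadership discussion is tied to assignment to CE.

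A second reply is that assigned-arm analysis cures the selection and is feasible. That is correct, but the article does not hold to it. Only the housing model speaks of assignment, and the other arm comparisons speak of strategy received.

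Three stronger readings are tempting, and the documents do not support them:

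- *The randomised comparison is broken.* It is exposed, not broken. Harm needs an actual refusal related to the arm, followed by exclusion, replacement or as-received analysis.
- *A lost site leaves its partner without a comparator.* The reach and adoption model compares with periods before treatment across staggered sites. It is not a matched-pair analysis, so balance suffers but a comparator remains.
- *The possible bias exceeds the stated 2.7-point detectable difference.* That figure is for either strategy against the period before CARE-VASH and is no yardstick between arms.

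**Conclusion.** The concern holds in conditional form and should be acted on. The stated order, with CE sites aware of their arm and carrying the extra peer time, allows refusal or delay to depend on the arm if the consent is the site's. With six blocks of two sites and a number of sites fixed by the funder, even one such loss matters. The mixed wording of the arm comparisons leaves open an analysis that would turn a refusal into selection bias.

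The magnitude of that bias cannot be given from the documents. The refusal probabilities rest on assumed rates, and the dilution to 5/6 on equal weights and a common effect. If the consent is only that of interviewees, the exposure is limited to the interview data, including the comparison of staff experience between arms, and does not reach the primary outcome.

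**What to change.** 1. State who consents and to what.
2. Obtain the agreement of each site's leadership to accept either arm, peer time included, before the arm is drawn or released. If this has already been done, say so.
3. State that all 12 sites are analysed as allocated, using the administrative data also for a site that declines or delays CE. Replace *received* by *assigned* in the arm comparisons in Study design, the sustainment analysis, the housing outcome and Acute care use. An analysis by strategy received can be supplementary.
4. Where prescribers, case managers and Veterans consent individually to baseline interviews, enrol them before the arm is disclosed. Peers are an exception, because they are sampled only at REP + CE sites.

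**Cost.** One start-up step is re-ordered and some sentences change; no further data are collected. The real price is that all 12 sites must discuss and provisionally commit peer time, although only six will use it.
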